## Abstract

**Background:**

Psychological distress is common in cancer survivors. Although there is some evidence on effectiveness of psychosocial care in distressed cancer patients, referral rate is low. Lack of adequate screening instruments in oncology settings and insufficient availability of traditional models of psychosocial care are the main barriers. A stepped care approach has the potential to improve the efficiency of psychosocial care. The aim of the study described herein is to evaluate efficacy of a stepped care strategy targeting psychological distress in cancer survivors.

**Methods/design:**

The study is designed as a randomized clinical trial with 2 treatment arms: a stepped care intervention programme versus care as usual. Patients treated for head and neck cancer (HNC) or lung cancer (LC) are screened for distress using OncoQuest, a computerized touchscreen system. After stratification for tumour (HNC vs. LC) and stage (stage I/II vs. III/IV), 176 distressed patients are randomly assigned to the intervention or control group. Patients in the intervention group will follow a stepped care model with 4 evidence based steps: 1. Watchful waiting, 2. Guided self-help via Internet or a booklet, 3. Problem Solving Treatment administered by a specialized nurse, and 4. Specialized psychological intervention or antidepressant medication. In the control group, patients receive care as usual which most often is a single interview or referral to specialized intervention. Primary outcome is the Hospital Anxiety and Depression Scale (HADS). Secondary outcome measures are a clinical level of depression or anxiety (CIDI), quality of life (EQ-5D, EORTC QLQ-C30, QLQ-HN35, QLQ-LC13), patient satisfaction with care (EORTC QLQ-PATSAT), and costs (health care utilization and work loss (TIC-P and PRODISQ modules)). Outcomes are evaluated before and after intervention and at 3, 6, 9 and 12 months after intervention.

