## Methods/Design

### Design

In this prospective randomized controlled trial in two parallel groups, patients are recruited by screening all LC and HNC patients, who visit the Department of Pulmonary Diseases or the Department of Otolaryngology and Head and Neck Surgery of the VU University Medical Center in Amsterdam, the Netherlands, for follow-up consultation at least one month after treatment, for distress using a computerized touch screen data collection system (OncoQuest) or by telephone using the Hospital Anxiety and Depression Scale (HADS). All patients who fulfil the in- and exclusion criteria are asked to participate. After stratification for tumour site (LC vs. HNC) and stage (stage I-II versus III-IV), 176 participating patients are randomly assigned to the intervention or control group. In order to assess efficacy, assessment before and after intervention takes place and at 3, 6, 9, and 12 months follow up.

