### Intervention

Patients in the experimental study arm enter a stepped care programme including 1) watchful waiting, 2) guided self-help via Internet or a booklet, 3) face-to-face problem solving treatment, 4) specialised psychological interventions such as cognitive behavioural therapy and/or antidepressant medication.

The basic proposition of stepped care is that all patients are offered the same low intensity (evidence-based) treatment as a first step. Only those patients, who do not recover, step up to a more intensive treatment. The HADS score is used to determine stepped-up levels of care. Stepping up to the next treatment level is indicated when a participant’s HADS-A or HADS-D score exceeds 7. The care coordinator controls the process, monitors the symptoms, and makes sure the patient steps up if necessary.

The stepped care programme in the present project includes the following four steps.

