#### Step 1: Watchful waiting

In the first step it is agreed on not to start intervention yet, but to wait for further development of symptoms. Because part of the patients recovers spontaneously [18] ‘watchful waiting’ is included in the multidisciplinary guideline on depression as first treatment step. Duration of the watchful waiting period in the present project including cancer patients is set on 2 weeks.

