#### Care as usual

Control group patients receive care as usual, which often means a single interview by a nurse or specialised intervention delivered by a social worker, psychologist or psychiatrist. In the context of the health economic evaluation, health care uptake is closely monitored, thus allowing for detailed post-hoc description of what usual care entailed exactly.

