### Statistical analyses

Descriptive statistics will be generated for the range of outcome variables, in particular to gauge whether randomization resulted in a balanced distribution of patients characteristics across the experimental conditions.

Repeated measures ANOVA will be used to determine the efficacy of intervention for continuous outcomes such as changes in HADS depression/anxiety symptom severity. Longitudinal changes over time in these variables will also be evaluation over all time points simultaneously using generalized estimating equations (GEEs). Analyses will be conducted in agreement with the intention-to-treat principle.

The economic data will be collected at baseline and follow-up and conducted as a cost utility analysis that is with health-related quality of life as the clinical endpoint. For the economic evaluation use will be made of the pertinent guidelines [39,44-46]. In other words, analyses will be conducted in agreement with the intention-to-treat principle; the societal perspective will be taken encompassing intervention costs, direct non-medical costs and indirect costs. Production losses will be economically valued using the friction cost method [47]. The time horizon will be set at one year, and therefore we will neither discount costs nor effects. Costs and effects will be analysed simultaneously, incremental cost-effectiveness ratios (ICERs) will be calculated and placed within 95% confidence intervals, 2,500 bootstrap replications of the ICERs will be projected on a cost-effectiveness plane, ICER acceptability curves will be plotted against different willingness-to-pay ceilings [48], and sensitivity analysis will be conducted as a matter of course focussing on uncertainty in the main cost-drivers. This will be done for the costs per QALY gained in a cost utility analysis.

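### Follow-up is timed from the end of an intervention whose length is set by HADS in the stepped-care arm and has no stated counterpart in the control arm

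*Protocol article*

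**What the plan says.** **Anchor of follow-up.** The Abstract (Methods/design) says "Outcomes are evaluated before and after intervention and at 3, 6, 9 and 12 months after intervention". The Design section says "assessment before and after intervention takes place and at 3, 6, 9, and 12 months follow up". It keeps an assessment tied to the end of the intervention but gives no time zero for the numbered months.

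**What sets the end of the intervention.** The Intervention section says "The HADS score is used to determine stepped-up levels of care", and "Stepping up to the next treatment level is indicated when a participant’s HADS-A or HADS-D score exceeds 7". It also says "Only those patients, who do not recover, step up to a more intensive treatment". The section on the main outcome measure names HADS as the primary outcome.

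**Step lengths.** For step 1, "Duration of the watchful waiting period in the present project including cancer patients is set on 2 weeks". Step 2 takes 5 weeks. Step 3 is six sessions with no stated interval. Step 4 is medication or referral for psychotherapy, with no stated length.

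**Control arm.** "Control group patients receive care as usual, which often means a single interview by a nurse"; the sentence goes on to name specialised care as the alternative. No end point is given.

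**Economic evaluation.** EQ-5D is taken at baseline and at the 12-month follow-up (Secondary outcomes). Under Statistical analyses, "The time horizon will be set at one year, and therefore we will neither discount costs nor effects".

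**The concern.** A parallel-group comparison needs a time zero that is defined in the same way in both arms and does not depend on what happens after randomisation. The anchor in the Abstract meets neither condition. In one arm it is reached when the primary outcome scale falls below a threshold, or when the steps run out. In the other arm it is not defined.

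Three things are at stake.

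- **Confounding with time.** The Background reports that psychological functioning gradually improves in the first year after cancer treatment, and patients can enter from one month after that treatment. If elapsed time differs between arms, part of any HADS difference reflects time and not the programme. Randomisation does not protect against this, because the timing is set afterwards. Repeated measures ANOVA treats visits as nominal occasions and does not correct for it.
- **Outcome-dependent timing within the arm.** Patients whose distress persists go through more steps and are therefore measured later than those who recover early.
- **The economic window.** The one-year horizon is the stated reason for not discounting. A window that starts at baseline and closes 12 months after the intervention ends is longer than a year and varies between patients.

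**Working it through.** **Scale of the trial (context, not in dispute).** The plan gives an effect size of 0.50, 80% power, 5% significance, 66 per group and 25% dropout.

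- Two-sided normal approximation: n = 2 × (1.96 + 0.842)² / 0.50² = 62.8, so 63 per arm. The t-test version gives 64. With 66 per arm, t-test power is 81.4%.
- Dropout: 132 / 0.75 = 176. The stated total is reproduced.

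**When the intervention ends.** I assume that the programme starts at baseline, that steps follow without a gap, and that a recovered patient's intervention ends with the step in which recovery is recorded. One month is 4.348 weeks. The time of the 12-month visit is 12 + (end week / 4.348) months from programme start.

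| Last step | End of intervention | 12-month visit, months from start | Basis |
|---|---|---|---|
| 1 | week 2 | 12 + 0.46 = 12.5 | stated |
| 2 | 2 + 5 = week 7 | 12 + 1.61 = 13.6 | stated |
| 3 | 7 + 6 to 7 + 12 = weeks 13 to 19 | 15.0 to 16.4 | assumed: six sessions, weekly to fortnightly |
| 4 | 13 + 8 to 19 + 26 = weeks 21 to 45 | 16.8 to 22.3 | assumed: a further 8 to 26 weeks |

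By the same formula, the 3-month visit falls at 3.5 or 4.6 months after exit from step 1 or step 2.

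**Spread within the stepped-care arm.** On stated durations alone it is 7 − 2 = 5 weeks. With the assumed lengths it is 11 to 17 weeks through step 3 and 19 to 43 weeks through step 4. A control patient timed from randomisation would be seen at 12.0 months.

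**Against the one-year horizon.** Under the Abstract's anchor, even the earliest leaver passes 12 months (12.5). The EQ-5D interval therefore exceeds one year for every stepped-care patient and differs between them. The Abstract and the Statistical analyses section cannot both hold as written.

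**Could the bias be sized?** A null simulation (no treatment effect) shows what would have to be assumed: HADS subscale mean 7, between-patient SD 3, correlation 0.5, within-patient SD 1.5 to 2.5, entry on either subscale above 7, and exits at weeks 2, 7, 13 and 26 (the last two assumed). A positive d favours stepped care.

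- Separate outcome score, no drift over time: d = 0.
- Drift of 0.05 points per week per subscale in both arms: d is about +0.27 to +0.39 if controls are read at week 2, about −0.14 to −0.17 if read at week 26, and about 0 if read at the stepped-care arm's mean exit time.
- Drift of 0.02: d is about +0.12 to +0.16 (week 2) and about −0.05 (week 26).
- Only the documented 5-week difference, applied to every patient, at drift 0.05: 2 × 0.05 × 5 = 0.5 HADS-total points, d about 0.09 to 0.11.
- If the HADS that triggers exit were itself used as the outcome, with no drift: d is about 0.11 to 0.24.

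Between 59% and 75% of simulated patients leave at the assumed week 26, so that input largely drives the figures that include it. The sign changes with the control visit date, which the document does not give.

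**The case against.** The best defence is that only one sentence, in the Abstract, ties the numbered months to the end of the intervention. The Design section, the EQ-5D schedule and the one-year horizon all fit months counted from baseline, so the Abstract may simply be loosely worded. A visit calendar by arm is also the kind of detail that an article leaves to the full protocol. Usual care can include specialised treatment, so controls are not without care. The Background gives no rate of improvement and adds that many patients remain or become distressed. Enrolment has no stated upper limit after cancer treatment, so some patients may be past the period of improvement.

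Much of this stands, and it rules out three stronger readings that a reader might infer:

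- **That the arms are in fact compared at different times.** How control visits are timed is not stated. The inference fails if they are matched to stepped-care visits, or if the post-intervention visit is one fixed date in both arms. Neither is written, but neither is excluded.
- **That regression to the mean enters one arm only.** This needs the stepping HADS to double as the outcome score, and the document does not say that it does.
- **That a spurious effect of known size follows.** The simulated values rest on assumed drift, step lengths and control timing, and they change sign.

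The defence does not remove the point itself. The anchor is stated outright and not merely left out, the Design section also keeps a post-intervention assessment, and reading the body as months from baseline leaves it in conflict with the Abstract.

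**Conclusion.** The concern holds in a limited form. As the Abstract states it, time zero for follow-up depends on the primary outcome scale in the stepped-care arm and is undefined in the control arm. On the document's own durations this moves time zero by 5 weeks between patients who leave after step 1 and after step 2, and it puts the 12-month visit at about 12.5 to 13.6 months from programme start. Later exits add an amount that the document does not state. This conflicts with the one-year economic horizon and, read literally, allows elapsed time to differ between arms while distress is changing. These figures rest on the programme starting at baseline and on steps following without gaps.

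A biased primary comparison has not been demonstrated: neither the size nor the direction of any bias can be fixed from the document. What is established is a badly fixed time zero and passages that must be reconciled.

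**What to change.** 1. Time every outcome assessment in both arms from randomisation, on the same dates (for example months 3, 6, 9 and 12), whatever step the patient has reached.
2. Replace the post-intervention assessment with one early visit at a fixed time from randomisation in both arms.
3. State that the HADS used for stepping is not the HADS analysed as the outcome.
4. Count costs and QALYs from randomisation to month 12, so that the one-year horizon and the decision not to discount hold.
5. Reconcile the Abstract, the Design section, the EQ-5D timing under Secondary outcomes and the Statistical analyses section with this schedule.

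The cost is an amendment to the visit schedule, with the same number of questionnaires and N unchanged at 176. The small downside is that some stepped-care patients will still be in treatment at the early visits. That is part of the strategy under test.

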**Discussion:**

Stepped care is a system of delivering and monitoring treatments, such that effective, yet least resource-intensive, treatment is delivered to patients first. The main aim of a stepped care approach is to simplify the patient pathway, provide access to more patients and to improve patient well-being and cost reduction by directing, where appropriate, patients to low cost (self-)management before high cost specialist services.

**Trial registration:**

NTR1868

## Background

Every year more than 14,000 patients are diagnosed with cancer, of whom 11,470 with lung cancer (LC) and 2,870 with head and neck cancer (HNC) in the Netherlands [1]. Five-year survival rates are estimated at 13% in LC and 50% in HNC. Approximately 80% of the LC patients are male compared to 65% of the HNC patients. Patients often have to deal with devastating side effects of initial treatment (surgery, radiotherapy, and/or chemotherapy), such as pain, fatigue, and respiratory, speech and swallowing problems, negatively affecting health-related quality of life and associated with increased levels of psychological distress. Co-morbid anxiety or depression is present in 20-30% of LC and HNC patients [2-4]. During the first year after treatment there is a gradual improvement of psychological functioning [5,6] but many patients continue to suffer from or develop anxiety or depression [2,7-9].

Because of the overwhelming evidence of psychological distress in LC and HNC patients, intervention is recommended in national guidelines. Some recent reviews have shown evidence on efficacy of psychosocial intervention in cancer patients in general [10,11]. Others question evidence mainly because randomized trials are scarce [12,13] and because most studies included all patients even those without symptoms of depression and anxiety. Furthermore, it appears that most intervention studies are applied in patients with breast cancer. Patients with less prevalent tumours such as HNC or poor survival rates as in LC are often not involved, while LC and HNC patients are among the most distressed patients compared to cancer patients in general [14].

In clinical practice at present, many cancer patients who report high levels of psychological distress are not taking advantage of psychosocial care [14,15]. Barriers to admission to adequate psychosocial care are a lack of adequate screening of anxiety and depression in the often very busy oncology settings, reluctance by patients to be referred because of the already long treatment period, and that traditional models of the delivery of psychosocial care cannot meet current demand. Other forms of delivery, such as brief therapies, group treatments and self-help, and a stepped care approach may provide useful alternatives. Studies regarding cost-effectiveness of psychosocial intervention in cancer patients are scarce [16].

Stepped care algorithms are based on clinically proven, best-practice pathways to care over a series of steps, while taking into account patients’ preference [17]. The steps involve watchful waiting, guided self-help and other brief therapies, followed by more intensive psychological interventions or medication. In stepped care, more intensive treatments are generally reserved for people who do not benefit from simpler first-line treatments, or for those who can be accurately predicted not to benefit from such treatments. The results of treatments and decisions about treatment provision are monitored systematically, and changes are made (‘stepping up’) if current treatments are not achieving a significant health gain [10]. Stepped care models have been developed for several health problems, including smoking, back pain, alcohol treatment, migraine, anxiety, eating disorders, methadone maintenance, and depression [10].

The main goal of the proposed study is to assess efficacy of a stepped care strategy compared to care as usual in patients with psychological distress after treatment for LC or HNC to improve psychological distress and thereby quality of life.

## Methods/Design

### Design

In this prospective randomized controlled trial in two parallel groups, patients are recruited by screening all LC and HNC patients, who visit the Department of Pulmonary Diseases or the Department of Otolaryngology and Head and Neck Surgery of the VU University Medical Center in Amsterdam, the Netherlands, for follow-up consultation at least one month after treatment, for distress using a computerized touch screen data collection system (OncoQuest) or by telephone using the Hospital Anxiety and Depression Scale (HADS). All patients who fulfil the in- and exclusion criteria are asked to participate. After stratification for tumour site (LC vs. HNC) and stage (stage I-II versus III-IV), 176 participating patients are randomly assigned to the intervention or control group. In order to assess efficacy, assessment before and after intervention takes place and at 3, 6, 9, and 12 months follow up.

### Study sample

Inclusion criteria are: treatment for UICC stage I-IV lung or head and neck carcinoma: ICD-10 C00-C14 (lip, oral cavity and pharynx), C32 (larynx), C33 (trachea), C34 (lung); psychological distress or possible or probable cases of depression or anxiety as assessed by the Hospital Anxiety and Depression Scale (HADS; HADS-D > 7 or HADS-A > 7 or HADS-total > 14).

Exclusion criteria are: other (neurological) diseases causing cognitive dysfunction; no motivation to undergo psychological therapy; current treatment for a depressive or anxiety disorder; end of treatment for a psychiatric disorder less than two months ago; high suicide risk; psychotic and/or manic signs; too little knowledge of the Dutch language to fill out the questionnaires.

### Randomization

Randomization is conducted centrally by an independent statistician, in blocks of two, stratified for tumour site (LC vs. HNC) and stage (stage I-II vs. III-IV), because these variables have prognostic relevance and need to be distributed evenly across both conditions.

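### Fixed blocks of two make about half of all allocations certain for anyone who knows the block size and the last allocation in the stratum, which seriously weakens allocation concealment

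*Protocol article*

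**What the plan says.** The Randomization section fixes both who allocates and how: "Randomization is conducted centrally by an independent statistician, in blocks of two, stratified for tumour site (LC vs. HNC) and stage". Its reason for stratifying is that both factors are prognostic and should be balanced between the arms. It does not say that block sizes vary or that the size is kept from recruiting staff.

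Other sections that bear on the point:

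- **Design:** "After stratification for tumour site (LC vs. HNC) and stage (stage I-II versus III-IV), 176 participating patients are randomly assigned". Recruitment is at "the Department of Pulmonary Diseases or the Department of Otolaryngology and Head and Neck Surgery of the VU University Medical Center in Amsterdam". Every patient who meets the criteria is to be approached.
- **Study sample:** entry rests on numeric HADS cut-offs, but one exclusion criterion is "no motivation to undergo psychological therapy".
- **Intervention and Care as usual:** stepped care is run by a coordinator ("The care coordinator controls the process, monitors the symptoms, and makes sure the patient steps up if necessary"). Controls receive whatever care is usual, with no sham. No masking is described.

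**The concern.** Two is the smallest possible block for 1:1 allocation, and it is the most predictable. Once the first patient of a block has been allocated, the arm of the next patient in that stratum is settled before anyone approaches that patient. If a recruiter can work this out, the invitation, the judgement about motivation or the timing of entry can shift with the arm that is due, even without intent. The arms could then differ in motivation or distress before treatment starts.

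Intention-to-treat analysis does not help, because the selection happens before randomisation. Adjustment for measured baseline factors can reduce the bias, but it cannot reach unmeasured factors such as motivation.

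**Working it through.** **Inputs from the protocol article.** Block size 2 and four strata, 2 sites × 2 stages (Randomization). Two arms (Design). 66 per group, 25% dropout, 176 in total (Sample size calculation). The 1:1 ratio is not stated but follows from blocks of two and equal groups.

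**The plan's own figure.** 66 / (1 − 0.25) = 88 per group, and 2 × 88 = 176, as stated. A two-sided 5% t-test with effect size 0.50 and 80% power needs 64 per group, so 66 is adequate (power 0.81). The sample size is not in dispute.

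**Certain allocations with blocks of two.** The possible blocks are AB and BA, so the second place is always forced.

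- Share forced = 1/2, and 0.50 × 176 = 88.
- Each stratum that ends on an odd number leaves one block half filled. The count is (176 − number of odd strata) / 2. Because 176 is even, 0, 2 or 4 strata can be odd, which gives 88, 87 or 86.
- Correct guesses: half of the first places and all of the second places, (0.5 + 1) / 2 = 0.75, and 0.75 × 176 = 132.

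**Other block sizes.** All permutations were enumerated, with the observer betting on the arm that has more places left. For block size b, the share forced is 1 / (b/2 + 1). The last row was simulated with four strata of 44 and the two sizes equally likely.

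| Scheme | Certain in advance | Correct guesses overall |
|---|---|---|
| Fixed 2 | 50% (88 of 176) | 75% |
| Fixed 4 | 33% (about 59) | 71% |
| Fixed 6 | 25% (44) | 68% |
| 4 and 6 at random, current size unknown to observer | about 6% (about 10) | about 69% |

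If the observer knew the current size in the 4-and-6 mix, a block of 4 would hold 4 × 1/3 = 1.33 forced places and a block of 6 would hold 6 × 1/4 = 1.5. That is 2.83 of 10, or 28%.

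**How easily the strata can be followed.** Tumour site corresponds to department, so each department has only two stage strata to track. The article's recruitment figures give 450 × 0.30 × 0.50 = 67.5 patients a year. If the strata were equal in size (an assumption), that is about 17 per stratum a year, or roughly one every three weeks.

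**The case against.** The strongest defence is that prediction needs knowledge the article does not give to recruiters. They would have to know the block size, the last allocation in the same stratum, and whether a block is open. The list is held centrally, the article does not say who enrols, and the first allocation in each block stays unpredictable.

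Visibility can also be questioned. Stepped care opens with two weeks of watchful waiting. Self-help is then coached by email or telephone, and problem solving treatment is given by a psychiatry nurse, not by the recruiting departments. Discretion at entry is limited too, since all eligible patients are to be asked and the HADS threshold is numeric. Finally, overall correct guessing improves only from 75% to about 69% under the remedy.

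Much of this stands, and it makes the finding conditional. It does not remove it. Position in the block is not a real barrier: two identical allocations in a row within a stratum reveal a block boundary. Hiding the list protects only what cannot be deduced from past allocations. The motivation criterion and the consent conversation remain open to judgement, and the article itself expects only half of distressed patients to agree. The modest change in overall guessing understates the gain, because what mostly disappears is certainty about the next arm.

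A reader might also infer that the self-reported primary outcome aggravates the problem. That is a separate bias, arising when patients know their treatment, and it would exist with any block size.

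**Conclusion.** The point holds as a serious weakness in allocation concealment. About half of all allocations (86 to 88 of 176) are certain in advance for an informed observer, who guesses 75% right overall. This rests on 1:1 allocation, on knowledge or inference of the block size, and on knowledge of the previous allocation in the same stratum. That the trial is unmasked is inferred from the treatments, though safely.

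Three stronger readings are not supported:

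- A reader might infer that concealment is defeated outright. It is not, because the first place in every block stays unpredictable.
- A reader might infer that every second patient in the trial can be predicted from the one before. That is true only within a stratum, and consecutive patients can fall in different strata.
- A reader might infer that selection bias took place. The article shows exposure to it, not its occurrence.

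**What to change.** For all allocations not yet made, replace the fixed block of two with randomly varying permuted blocks, for example of 4 and 6, within each of the four strata. The sizes should be known only to the independent statistician and not disclosed to recruiting staff.

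The cost is a new list and slightly looser balance. The end-of-recruitment imbalance is at most 3 per stratum instead of 1, so at most 4 × 3 = 12 overall. Relative to equal groups, the information kept is then 1 − (12/176)² = 0.995, which is negligible for power.

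The article does not state recruitment status. If allocation is already complete, report the block size as a limitation and compare baseline characteristics of first-in-block and second-in-block patients by arm. That comparison can reveal selection on measured factors but cannot rule it out on unmeasured ones.

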### Sample size calculation

To demonstrate an effect size of 0.50 (based on a meta-analysis on psychological treatment in mild depression), 66 patients are needed in each group (power 80%, significance level 5%) [49]. Taking into account a dropout of 25%, in total 176 patients will be included. With an annual intake of 450 LC and HNC patients, 30% having psychological distress, and 50% willing to cooperate, and an inclusion period of 2.5 years, feasibility of the study is guaranteed.

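### The HADS efficacy analysis names no adjustment for baseline HADS or for the stratification factors; prespecifying both would be a free gain in precision

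*Protocol article*

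**What the plan says.** The Randomization section allocates patients "in blocks of two, stratified for tumour site (LC vs. HNC) and stage (stage I-II vs. III-IV"), and gives the reason: "because these variables have prognostic relevance and need to be distributed evenly across both conditions".

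The Statistical analyses section states the efficacy method: "Repeated measures ANOVA will be used to determine the efficacy of intervention for continuous outcomes such as changes in HADS depression/anxiety symptom severity". It adds GEE over all time points and the intention-to-treat principle. It lists no covariates for either model and excludes none.

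The Design section places a HADS assessment before the intervention, one after it, and further ones at 3, 6, 9 and 12 months. Baseline HADS is therefore available, and so are site and stage, which are needed to randomise.

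The Sample size calculation section sizes the trial as a plain two-group comparison and claims no credit for covariates: "To demonstrate an effect size of 0.50 (based on a meta-analysis on psychological treatment in mild depression), 66 patients are needed in each group", then "Taking into account a dropout of 25%, in total 176 patients will be included".

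**The concern.** Two sources of precision are in hand but do not appear in the stated analysis.

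- **Baseline HADS.** In its usual form, repeated measures ANOVA on changes reads the treatment effect from the change since baseline. That fixes the coefficient on baseline at 1. A baseline-adjusted comparison estimates the coefficient, and its variance is never larger apart from one degree of freedom.
- **Tumour site and stage.** Stratifying balances these factors and so reduces the true variance of the treatment difference. A model without them still counts their variance as noise. Its standard error is then too large and its test slightly conservative.

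At stake are wider confidence intervals than the data would allow and some avoidable loss of power. Neither point biases the treatment estimate.

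**Working it through.** **1. Reproduce the sample size.** Inputs from the Sample size calculation section: d = 0.50, 80% power, 5% level (taken as two-sided), 66 per group, 25% dropout. A two-sample t-test needs 64 per group, and 66 per group gives 81.4% power. Dropout: 66/0.75 = 88 per group, 2 × 88 = 176. The plan's figures stand.

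**2. Baseline HADS.** Take the follow-up SD as 1 and assume an equal baseline SD and one follow-up. rho is not in the document, so a range is shown.

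- Variance of the change score: 2(1 − rho)
- Variance after baseline adjustment: 1 − rho²
- Ratio, adjusted to change: (1 − rho²)/[2(1 − rho)] = (1 + rho)/2

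Power by t-test, 66 per group, standardised effect 0.50/√variance:

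| rho | Var. change | Var. adjusted | Ratio | Power, change | Power, adjusted | Gain (points) |
|---|---|---|---|---|---|---|
| 0.3 | 1.40 | 0.91 | 0.65 | 67.4% | 84.8% | 17.4 |
| 0.4 | 1.20 | 0.84 | 0.70 | 74.0% | 87.5% | 13.5 |
| 0.5 | 1.00 | 0.75 | 0.75 | 81.4% | 90.9% | 9.5 |
| 0.6 | 0.80 | 0.64 | 0.80 | 89.0% | 94.6% | 5.6 |
| 0.7 | 0.60 | 0.51 | 0.85 | 95.7% | 97.9% | 2.2 |

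Under these assumptions the change score drops below 80% only when rho is under about 0.48.

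**3. Unequal SDs.** If the baseline SD is k times the follow-up SD, the change-score variance is 1 + k² − 2·k·rho. The adjusted variance stays at 1 − rho². At rho = 0.3:

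- k = 0.8: variance 1.16, power 75.4%
- k = 0.7: variance 1.07, power 78.7%
- k = 0.6: variance 1.00, power 81.4%

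Against 84.8% adjusted, the gain is then about 9, 6 and 3 points instead of 17.

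**4. Several follow-ups.** Assume the same effect at all five follow-ups and equal correlations. The five-visit mean has variance (1 + 4·rho)/5. Subtracting baseline adds 1 − 2·rho; adjusting for baseline subtracts rho².

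- rho = 0.3: 0.44 + 0.40 = 0.84 for change (87.5% power); 0.44 − 0.09 = 0.35 adjusted (99.8%)
- rho = 0.5: 0.60 + 0 = 0.60 for change (95.7%); 0.60 − 0.25 = 0.35 adjusted (99.8%)

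Power is above 80% either way, but the adjusted variance is still much smaller.

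**5. Stratification factors.** Let site and stage explain a share R² of the variance (assumed; not in the document). With stratified allocation, the true variance is multiplied by 1 − R², while the unadjusted model still estimates 1. Normal approximation, 66 per group:

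| R² | Actual type I error, unadjusted | Power, unadjusted | Power, adjusted |
|---|---|---|---|
| 0.02 | 4.8% | 82.2% | 82.7% |
| 0.05 | 4.4% | 82.5% | 83.8% |
| 0.10 | 3.9% | 83.2% | 85.7% |

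The gain is about 0.5 to 2.5 points. Most of the benefit therefore comes from the handling of baseline HADS, not from the strata.

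**The case against.** The strongest reply is that the document is only silent. A journal article condenses the protocol, covariate lists are commonly left to the analysis plan, and both named methods can carry covariates. This stands against any claim that the trial has decided to leave adjustment out: a reader might infer that from the text, but the document does not say so. It does not dispose of the point, because the section does commit to a method and to changes as the quantity analysed. As usually run, that is the less efficient use of baseline.

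A reader might also infer that the trial misses its 80% power. The document does not support this. The shortfall appears only with rho below about 0.48, equal SDs and a single follow-up, none of which the document states. Selection on high HADS might lower rho, but it would also narrow the baseline SD, and step 3 shows that this recovers most of the loss. How much the range narrows is itself unclear, since the entry criteria are alternatives: "HADS-D > 7 or HADS-A > 7 or HADS-total > 14". One subscale score of 8 is enough, so eligible totals start at 8. Averaging the five follow-ups also lifts the change contrast above 80% at rho 0.3.

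Finally, baseline HADS is not ignored, and the strata by themselves matter little. Both statements are correct. Under every assumption tried, baseline adjustment still did at least as well as the change score.

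**Conclusion.** The point holds as an efficiency improvement, not as an error. The stated analysis names no adjustment for baseline HADS, or for two factors that the protocol itself calls prognostic.

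- **Baseline HADS:** about 2 to 17 power points at 66 per arm for rho 0.7 down to 0.3, with equal SDs and one follow-up. The gain is smaller if the baseline SD is the narrower one.
- **Site and stage:** about 0.5 to 2.5 points for R² of 0.02 to 0.10. Without them the type I error is 4.8% to 3.9%, so the test is conservative but valid.

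Both rho and R² are assumed ranges. The sample size of 66 per group and 176 in total is sound and does not depend on this point.

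**What to change.** Add one sentence to the Statistical analyses section: follow-up HADS scores are modelled longitudinally, with baseline HADS, tumour site (LC/HNC) and stage (I-II/III-IV) as prespecified covariates. The GEE already named can carry these terms, with the follow-up visits as outcomes and baseline as a covariate. Apply the same rule to the continuous secondary scales, each with its own baseline where one is measured.

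This needs no extra patients, visits or data, and the sample size is unchanged. The model spends only a few degrees of freedom, and the covariates are fixed before results are seen.
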